### Statistical methods

Data is entered into dedicated databases and statistical analysis will be performed using STATA13 [49]. Cleaning and data management will be carried out on all relevant datasets and all statistical analysis will be performed using the ‘intention to treat’ principle. Descriptive statistics will be used to describe baseline variables. Differences in change in mean scores from baseline to follow-up between the two groups for continuous variables will be tested using unpaired t-tests provided they are normally distributed. Non-parametric tests will be performed for non-normally distributed data. Multiple regression analysis will be undertaken to check for interactions between gender, age and socio-economic background. For dichotomous variables, chi-square tests or logistic regression will be performed. Readmissions and survival will be analysed using Cox regression analysis.

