## Methods/Design

### Design

LC-REHAB was launched in three hospital units in Regional Hospital West Jutland (RHWJ), Denmark as an open randomised parallel group controlled study within which participants are allocated to either the intervention arm (LC strategies incorporated in standard CR) or to the control arm (standard CR). The randomisation is computer generated in a 1:1 ratio stratified for hospital unit, diagnosis (IHD or HF) and gender, alternating in blocks of two to four. According to power calculations, a total of 750 patients were needed to be recruited for the primary analysis. For secondary analysis of body compositions with Dual energy X-ray absorptiometry (DXA) scans, n = 150 patients were needed.

The CR program in both the intervention and control arms lasts for eight weeks, with training sessions three times a week and one education session per week. All sessions last 1.5 hours. In total, there are 24 training sessions and eight education sessions. The education in both arms is divided into eight topics; one topic per week. The topics are: function and symptoms of the heart, lifestyle effects on the development of IHD and HF, emotional reactions, medication, tiredness, the importance of relatives or other networks, importance and types of exercise, and future life with a chronic disease. The topics were elected on a theme day by LC educated health professionals and experienced patients with ‘The Disease Management Program for cardiovascular disease’ from Central Denmark Region as a general framework [18]. The training sessions are conducted by a physiotherapist in the presence of a nurse in case patients become unwell. The sessions consist of both cardio-stress and muscle-strengthening exercises. The education sessions are presented mainly by a nurse except for the topics on exercise and future life which are presented by the physiotherapist. In each arm of the study, patients are supported by the same team of nurse and physiotherapist throughout the eight week period.

Data is collected four times: at baseline, just after finishing the eight week CR program, three months after program completion, and at three years after program completion. A bicycle exercise test is conducted at all four data collection points (Figure 1).

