### Power calculations

From an existing CR database in RHWJ the standard deviation (sd) on the change in the SF-12 scales was known. It is expected that better coping ability could affect the scales ‘vitality’ (sd = 24.4 percentage points) and ‘mental health’ (sd = 13.4 percentage points). Necessary participant numbers were calculated under different assumptions which led us to choose a sample size of minimum 750 patients. If all patients complete the program, a difference in vitality of 5 percentage points and a difference in mental health of 2.75 percentage points will be detected with a power of 80% and a p-value of 0.05. With a dropout of 10 and 20% respectively, a difference in vitality of 5.3 and 5.6 respectively, and a difference in mental health of 2.9 and 3.1 respectively, will be found under the same assumptions.

From in vivo precision of DXA scans a sd of 0.187 in total body fat (TBF) at two consecutive measures was known [48]. We will include at least 150 patients to receive DXA scans in this study. Selection was based on the computer generated randomisation, thus every fourth participant was allocated for DXA scan – stratified for two hospital units, gender and diagnosis. If all 150 patients attend the DXA scan a difference of 0.09 kg in TBF will be able to be shown with a power of 80% and a p-value of 0.05.

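### Unpaired t-tests on change, with a normality-triggered switch to rank tests, are valid but give up precision that ANCOVA on baseline and the randomisation strata would recover at no cost

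*Protocol article*

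**What the plan says.** The Design section describes 1:1 randomisation "stratified for hospital unit, diagnosis (IHD or HF) and gender, alternating in blocks of two to four". With three hospital units, two diagnoses and two genders that makes 12 strata. The same section makes baseline the first of four data collections.

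The Statistical methods section then fixes the tests:

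- Continuous outcomes: "Differences in change in mean scores from baseline to follow-up between the two groups for continuous variables will be tested using unpaired t-tests", on condition that the data are normal. Otherwise, "Non-parametric tests will be performed for non-normally distributed data".
- Multiple regression has one stated job, which is to look for interactions involving age, gender and socio-economic position.
- Dichotomous outcomes get either a chi-square test or a logistic model, with no rule for choosing and no covariates named.
- "Readmissions and survival will be analysed using Cox regression analysis", again with no covariates or stratification named.

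Hospital unit and diagnosis do not appear in that section, and gender appears only in the interaction check.

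The Power calculations section says that "the standard deviation (sd) on the change in the SF-12 scales was known", gives "sd = 24.4 percentage points" for vitality and 13.4 for mental health, and arrives at "a sample size of minimum 750 patients" for differences of 5 and 2.75 points "with a power of 80% and a p-value of 0.05".

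**The concern.** The trial collects a baseline value for most continuous outcomes and randomises within 12 strata, yet the effect analysis for those outcomes makes limited use of the first and none of the second.

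Three features matter:

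- A change score uses baseline, but with its coefficient set to 1 and not estimated. Unless the correlation between baseline and follow-up is close to 1, this leaves avoidable noise and chance baseline imbalance in the comparison.
- Stratified randomisation balances the arms on prognostic factors. An analysis that omits those factors computes its standard error as if that balance had not been imposed, so the standard error is too wide when the factors predict the outcome.
- Letting the observed distribution decide between a comparison of means and a rank test makes both the test and the quantity estimated depend on the data. The rank test also gives no adjusted mean difference.

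What is at stake is efficiency: the same patients could give a more precise estimate that reflects the design.

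**Working it through.** **Inputs.** From Power calculations: SD of change 24.4 (vitality) and 13.4 (mental health); differences 5 and 2.75; alpha 0.05, power 80%, N = 750, so 375 per arm. Two-sided testing is assumed, and it reproduces the stated figures. The correlation ρ between baseline and follow-up is not in the protocol; it is assumed to lie between 0.3 and 0.9, with equal variances at both times.

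**Step 1: reproduce the plan.** With n per arm = 2(1.96 + 0.8416)² × SD²/δ²:

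- Vitality: 2 × 7.849 × 24.4²/5² = 373.8, so 374 per arm and 748 in total.
- Mental health: 2 × 7.849 × 13.4²/2.75² = 372.7, so 373 per arm and 746 in total.

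At 375 per arm the power is 80.1% and 80.2%. Detectable differences are 4.99 and 2.74 with no dropout, 5.26 and 2.89 at 10% dropout, and 5.58 and 3.07 at 20%. These match the stated 5 and 2.75, 5.3 and 2.9, 5.6 and 3.1. The sample size is right for the planned test.

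**Step 2: effect of estimating the baseline coefficient.** With variance s² at each time:

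- Var(change) = 2s²(1 − ρ)
- Residual variance in ANCOVA = s²(1 − ρ²)
- Ratio = (1 + ρ)/2

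For vitality, power = Φ(5/(24.4 × √(2 × ratio/375)) − 1.96), and detectable difference = 4.99 × √ratio.

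| Analysis | Variance ratio | Power for 5 points, N = 750 | Detectable difference | N for 80% power |
|---|---|---|---|---|
| t-test on change | 1 | 80.1% | 4.99 | 748 |
| ANCOVA, ρ = 0.3 | 0.65 | 93.6% | 4.02 | 486 |
| ANCOVA, ρ = 0.5 | 0.75 | 90.0% | 4.32 | 562 |
| ANCOVA, ρ = 0.7 | 0.85 | 86.1% | 4.60 | 636 |
| ANCOVA, ρ = 0.9 | 0.95 | 82.1% | 4.87 | 712 |

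Mental health behaves the same way: 93.6%, 90.1%, 86.2% and 82.2% power, against 80.2%.

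Under the plan's 20% dropout scenario (300 per arm) the standard error is 24.4 × √(2/300) = 1.992. Power for 5 points on change is Φ(2.51 − 1.96), about 71%. ANCOVA gives about 83% at ρ = 0.5 and 78% at ρ = 0.7.

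**Step 3: effect of the strata.** This was simulated with 12 equally likely strata, permuted blocks of 2 or 4, N = 750, ρ = 0.5 and 2,000 runs per setting (Monte Carlo error about half a percentage point on a 5% rate).

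| Share of change variance due to strata | t-test on change: type I error | t-test on change: power | ANCOVA with baseline and strata: type I error | ANCOVA with baseline and strata: power |
|---|---|---|---|---|
| 0% | 5.1% | 81% | 5.1% | 89% |
| 5% | 4.0% | 78% | 4.1% | 91% |
| 10% | 3.5% | 77% | 5.0% | 90% |
| 20% | 2.5% | 73% | 5.3% | 90% |

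The simulation holds the SD within strata at 24.4, so the overall SD grows with the share due to strata, and that is why the t-test's power falls below 80%. If 24.4 is already the SD across all strata, the planned power does not fall. At a 10% share it is Φ((2.806 − 1.96)/√0.90), about 81%, where 2.806 = 5/1.782 and 1.782 = 24.4 × √(2/375). Either way the unadjusted test is conservative and the adjusted one is more precise.

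**Step 4: programme completion.** There is no baseline value, so only the strata can help. An illustration with 80% completion and an odds ratio of 1.7 (both assumed) shows no difference if the strata are not prognostic. With a between-strata SD of 1 on the logit scale, the chi-square test has 3.5% type I error and 74% power, against 4.7% and 78% for a stratified (Mantel-Haenszel) test.

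**The case against.** The best defence is that nothing here is an error. The t-test on change is unbiased under randomisation, the sample size was built on the SD of that change, and Step 1 shows that the plan delivers the power it states. All of that stands.

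Four stronger readings are tempting, and the protocol does not support them.

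- *That the plan ignores baseline.* It does not: subtracting baseline is a use of it, with the coefficient fixed. Differencing also removes any stratum effect that is constant over time, so factors that predict the level of SF-12 need not predict its change.
- *That the gain reaches the primary outcomes.* Those are adherence, morbidity and mortality. Completion, session attendance, readmission and survival have no baseline value, so the factor (1 + ρ)/2 applies to none of them. It applies to quality of life and to lifestyle and risk factors, which are secondary, although two SF-12 scales drive the sample size.
- *That the strata are excluded from the logistic and Cox models.* The article names no covariates for either. That is silence, and such detail may sit in an analysis plan that is not shown. Logistic regression is expressly allowed. What the article does is leave the chi-square test open as an equal alternative.
- *That diagnosis and hospital are strong predictors.* This is plausible, but the protocol gives no figure.

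The switch to rank tests is at least declared in advance. At about 375 per arm the t-test hardly needs it. That argument is weaker for the DXA subset of 150 patients, about 75 per arm.

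**Conclusion.** The point holds as an efficiency improvement. For continuous outcomes the article commits to a valid but less precise analysis than the collected data allow, and to a test that depends on the observed distribution.

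The size depends on two quantities that the protocol does not give. One is ρ: the gain in power for 5 vitality points runs from about 14 percentage points at ρ = 0.3 to about 2 at ρ = 0.9, assuming equal variances. The other is how prognostic the strata are: with none of the variance due to strata, omitting them costs nothing; with 10 to 20%, the simulated type I error of the unadjusted test falls to about 3.5 to 2.5%.

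A reader might infer that the trial is underpowered or at risk of false positives. Neither follows. The stated N and power are reproduced, and omitting prognostic strata makes the test conservative.

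**What to change.** Amend the Statistical methods section as follows.

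- For continuous outcomes with a baseline value, make the effect analysis an ANCOVA or mixed model of the follow-up value on arm, baseline value, hospital unit, diagnosis and gender.
- Drop the normality-triggered switch. Use robust or bootstrap standard errors for skewed scales, and take more care with the DXA subset, where numbers are smaller.
- For programme completion, choose logistic regression with the three stratification factors over the chi-square option.
- State that the Cox models for readmission and survival are adjusted for, or stratified by, the same factors.

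The cost is about one paragraph of wording, settled before the outcome data are analysed. All the variables are already collected, and no patients or visits are added.

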### Ethical considerations

The intervention carries no risks and all patients will have at least standard treatment. The participants will only be included in the study, if they give written consent after verbal and written information. All patients will participate on a voluntary basis and will be informed that they at any time can withdraw their informed consent. The study will be carried out in agreement with the Declaration of Helsinki II and in accordance with Good Clinical Practice. The study has been approved by the Ethical Committee of Central Denmark Region (journal number 20100230).

## Discussion

In the future, increasing numbers of people will have to live with a chronic heart condition. Cardiac rehabilitation is thus of great significance due to its known potential to reduce morbidity and mortality and improve quality of life. Different patient education methods have been developed to address the challenges of non-adherence to CR programs and limited success with lasting lifestyle improvements. In the LC-REHAB study, the effect of a new patient education strategy; learning and coping, in addition to standard CR is evaluated on morbidity, mortality, adherence, quality of life plus lifestyle and risk factors. To understand the study design and rationale more comprehensively, knowledge of LC and the theory underlying its strategies is required. This paper combines a description of LC strategies and their theoretical basis along with the LC-REHAB study protocol.

Patients are followed up to three years after they have finished CR. This will provide insight into the long-term effect of CR and especially the effect of the LC strategies. The study is un-blinded. Combined with the self-reported information of quality of life, diet, smoking and exercise this may lead to differential misclassification.

This paper aims to provide knowledge and transparency of the theories behind LC strategies. The hypothesis is that LC strategies applied in CR can enhance adherence in CR and thus lead to reduced morbidity, morbidity and readmissions, and improve quality of life for patients with IHD or HF. Additionally, the results of the study will be a significant contribution to the development of relevant evidence-based guidelines for effective CR.

## Abbreviations

CPR: Central person register
CR: Cardiac rehabilitation
DXA: Dual energy X-ray absorptiometry
HDL-cholesterol: High-density lipoprotein cholesterol
HF: Heart failure
IHD: Ischemic heart disease
LC: Learning and coping
LDL-cholesterol: Low-density lipoprotein cholesterol
MI: Motivational interviewing
QALY: Quality-adjusted life years
RHWJ: Regional Hospital West Jutland
SD: Standard deviation
SF-12: Short form-12
TBF: Total body fat
WHO: World Health Organization.
